### **Preliminary analyses and data cleaning**

At completion of data collection, all variables and all logical pairs of variables will be subject to descriptive analyses using graphs, frequency counts and summary statistics. This will allow a) identification of unusual or unexpected results for data checking and b) familiarisation with the distributions and associations within the data set. Outcome variables which have severely non-symmetric distributions will be either transformed or categorised.

At the completion of data checking and correction, the data set will be locked for analysis.

### **Checking for homogeneity of study centres**

As this is a multi-centre study, early analyses will address the question of whether or not there is heterogeneity between centres. Linear models will be fitted to each outcome measure in turn, with centre and centre by treatment added as fixed effects. Any statistically significant differences will be documented and explored further for potential confounding with demographic or medical history factors. If variation between centres cannot be explained (or is shown to be related to differences in study methods), the primary analysis will continue as planned, but will be followed by sensitivity analyses which will either stratify by or exclude the outlier site(s) (depending on the sample size of the site(s) involved).

### **Demographic and baseline characteristics**

The demographic and medical characteristics of participants in each treatment group will be summarised using percentages or means and standard deviations. Pearson's Chi-square and independent samples t-tests will be used to check for any statistically significant differences

between groups. Results will be documented as p-values and, where necessary, addressed within the interpretation of study results.

### **Missing data and protocol violations**

In the case of death, all measurements prior to death will be included in the analysis but all after death will be set to missing. To address withdrawals, loss to follow-up or non-compliance with the study analyses will be conducted on both an intention to treat (ITT) and per protocol (PP) basis. Withdrawing and non-compliant participants shall be encouraged to continue with data collection even if stopping treatment. Where data items are missing the last value carried forward method to replace missing data in the ITT analysis will be used. Participants who have significant deviations from the protocol will be removed from the PP analysis after the completion of the ITT analysis. Such significant deviations from the protocol will be determined and documented by the study clinician during the course of the study. Any deviation from randomisation, missing data and withdrawals will be fully reported for this purpose.

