#### 3.2 Sample

##### Sample Size

Following the release of the Phase II SLT trial results, sample size for this study was recalculated as the two studies used very similar participant cohorts and study design. In particular, the Phase II study provided useful data for VADAS-cog, one of the primary outcomes for the current study. Sample size was calculated using the Phase II trial outcome data for the two primary measures (VADAS-Cog and ADCS-ADLs). Based on their VADAS-Cog data, we expect the minimum between-group endpoint to be 3 or more units (with a standard deviation of 6.56) for a clinically meaningful change in cognition. Using a one-sided independent samples t-test for the purpose of calculating sample size, a total of 166 participants are required to detect this difference with 90% power at the 0.05 significance level. For the ADCS-ADLs, we anticipate the minimum between-group endpoint to be 3 or more units (with a standard deviation of 5.31) for a clinically meaningful change in daily functioning. Using a one-sided independent samples t-test for the purpose of calculating sample size with this measure, a total of 110 participants are required to detect this difference with 90% power at the 0.05 significance level. Allowing for a total non-compliance/withdrawal rate of 30%, 238 participants will be recruited into the trial across all centres to ensure 166 participants in the final analyses.

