## **Drug Accountability**

On an ongoing basis all study drugs will be reconciled against delivery, use and returned medication documents. Study drugs which are not used may be destroyed in a suitable facility locally after drug accountability has been completed and with confirmation from the coordinating chief investigator. To be compliant with the treatment protocol study, drug dosing must have a compliance rate of at least 70% over the 52-week study period. Treatment compliance will be calculated by dividing the actual number of capsules taken with expected number of capsules to be taken for the treatment period and multiplying by 100. Self-reported measures of compliance will involve asking participants and their study partner/carer to complete a diary between visits. The researchers will also ask about their adherence to the prescribed treatment regime at the week 4, 13, 26, 39 and 52 visits.

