### **Primary efficacy analysis**

The primary analysis will be linear mixed models through which we will test for differences between treatment groups on each outcome over time, with adjustment for random variation between treatment centres, with and without adjustment for other potentially important predicts (e.g. compliance, age, gender, severity of VaD). Non-linear changes over time will be tested by a) fitting time as categorical variable and b) testing for quadratic and cubic effects. Results will be reported as regression coefficients (or odds ratios if categorical) and associated 95% confidence intervals.

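### Up to four versions of the primary analysis (ITT or per-protocol, with or without covariates, one named covariate being post-randomisation compliance) stand side by side, with no rule for which decides

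*Protocol*

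**What the plan says.** Section 5.2, Missing data and protocol violations, states that "analyses will be conducted on both an intention to treat (ITT) and per protocol (PP) basis". Missing items in the ITT analysis are filled by last value carried forward. Participants with significant deviations, as judged by the study clinician, are taken out for the per-protocol (PP) analysis once the ITT analysis is finished.

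Section 5.2, Primary efficacy analysis, defines the primary analysis as linear mixed models that test for group differences over time, "with and without adjustment for other potentially important predicts". The examples given are compliance, age, gender and severity of VaD. Results are reported as coefficients with "associated 95% confidence intervals".

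Section 3.2, Sample Size, says that "238 participants will be recruited into the trial across all centres to ensure 166 participants in the final analyses", after an allowance of 30% for non-compliance and withdrawal together. It names no analysis set.

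Drug Accountability, in section 3.3, says that "drug dosing must have a compliance rate of at least 70% over the 52-week study period". The definition of the PP set in 5.2 does not refer to this threshold.

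**The concern.** Two binary choices, analysis set and covariates, give four results per primary scale. Both covariate versions sit inside what the protocol calls the primary analysis. The only link between ITT and PP is the order in which they are run. No version is called supportive, and no agreement between versions is required. Fixing the scale, the visit and the shape of time would leave this choice open.

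Three things make it more than a labelling matter:

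- The PP set is formed after randomisation, so differential compliance or withdrawal can bias it.
- Compliance as a covariate puts a post-randomisation variable into a model that counts as primary.
- The covariate list is open, so more than one adjusted model is possible and four is not an upper limit.

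If the versions disagree in a borderline result, the protocol gives no rule for which one stands.

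**Working it through.** **The plan's own figures.** Section 3.2 states "we expect the minimum between-group endpoint to be 3 or more units (with a standard deviation of 6.56", with the design condition "Using a one-sided independent samples t-test for the purpose of calculating sample size", 90% power and the 0.05 level. The exact t-test gives 82.6 per arm, so 83 per arm and 166 in total. For ADCS-ADL (3 units, SD 5.31) it gives 54.3 per arm, so 55 and 110. With 30% loss, 166/0.70 = 237.1, which becomes 238 with equal arms. All three figures reproduce and are not in dispute.

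**Inputs for the false-positive rate.**
- PP share of ITT: f = 0.70, using the plan's 30% loss as a proxy (166/238 = 0.697).
- Share of outcome variance explained by the covariates: R². The protocol gives none, so 0.1 to 0.5 is assumed.
- Level: one-sided 5% (the sample-size basis) and two-sided 5% (the 95% intervals).
- PP exclusion unrelated to outcome.
- Success claimed if any one version is significant.

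**Choice of set alone.** The correlation of the ITT and PP statistics is √f = √0.70 = 0.837. The chance under no effect that at least one of two standard normal statistics with this correlation crosses its limit is 7.3% one-sided and 7.6% two-sided.

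**Set and covariates.** The correlation of the unadjusted and adjusted statistics is taken as √(1 − R²), and the cross terms are products of the two correlations. The chance that at least one of the four is significant is:

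| R² | one-sided 5% | two-sided 5% |
|---|---|---|
| 0.1 | 9.1% | 9.7% |
| 0.3 | 10.5% | 11.3% |
| 0.5 | 11.4% | 12.4% |

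A simulation of the four ordinary regressions at N = 238 and f = 0.70 gave 9.9%, 11.4% and 12.7% two-sided. With f = 0.90 and R² from 0.1 to 0.5 the two-sided calculation gives 8.3% to 10.6%. Four independent tests would give 1 − 0.95⁴ = 18.5%, which does not apply here because the versions are strongly correlated.

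**When the covariate factor applies.** The √(1 − R²) term suits a treatment effect on a post-baseline value. In a random-intercept model with baseline and weeks 26 and 52, N = 238 and complete data, main-effect covariates left the group-by-time statistic unchanged to five decimals (−1.49252 in both). With 30% missing at week 52 the correlation between the two statistics was 0.99. In that model the four versions are in effect two, and the 7-8% figure is the relevant one.

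**How often PP would stand alone.** Take the same true effect d in both sets, SD 6.56 and a limit of z > 1.96. The expected statistic is d / (6.56 × √(4/N)). At d = 2 this is 2.35 for N = 238 and 1.96 for N = 166. At d = 3 it is 3.53 and 2.95. With correlation √(166/238) = 0.835:

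| True effect | ITT only | PP only | Any disagreement |
|---|---|---|---|
| 2 points | 18.5% | 3.4% | 21.9% |
| 3 points | 11.2% | 0.8% | 12.0% |

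**The case against.** **ITT is evidently meant to lead.** It is completed first, it alone has a rule for missing values, and the two sets are introduced as a way of handling withdrawal and non-compliance. This is a natural reading, and equal standing of the two sets is itself only an inference. But order of work is not rank, and the wording of the primary analysis still holds both covariate versions.

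**Ranking belongs in the statistical analysis plan.** It often does, and an unseen plan may settle it. Here, however, the protocol is not silent: it puts competing versions under the primary analysis and names compliance among the covariates. A later plan would have to override that text.

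**A reader might infer that the false-positive rate is simply about twice nominal.** The documents do not support that as a plain statement. They nowhere say that one significant version suffices. If all four had to be significant, the rate would be at or below 5%. The upper figures also need covariates that alter the treatment test. The protocol mentions random variation between centres but specifies no participant-level effect and no covariate-by-time terms, so it does not settle whether they would.

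**A reader might infer that PP would often carry the claim,** because ITT and PP disagree in about 22% of trials at 2 points. Most of that is ITT significant and PP not, which follows from the smaller PP sample. The direction that matters is 3.4%.

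**A reader might take 166 as a per-protocol count.** Section 3.2 names no set, and 166/0.70 is a routine inflation for attrition. What stands is that ITT with values carried forward would not ordinarily shrink from 238 to 166, so the set needs naming.

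**Part of the remedy exists.** Deviations are to be documented during the study, analysts are blinded, and a 70% compliance threshold is stated. The PP definition does not use that threshold.

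**Conclusion.** The point holds in a limited form. The protocol sets up to four versions of its primary analysis side by side, allows a post-randomisation covariate, leaves the covariate list open and gives no deciding rule. The cost is conditional on any one significant version being claimable: about 7-8% instead of 5% for one scale and visit from the choice of set, and about 9-12% if the covariates also change the treatment test. These figures assume a PP set of 70% of ITT, R² of 0.1-0.5 and PP exclusion unrelated to outcome. Informative exclusion could add bias beyond them. If carried-forward values vary less than observed ones, ITT and PP are more strongly correlated and the inflation is smaller. A PP-only success is rare under a true effect, about 3% at 2 points and 1% at 3. The change is worth making because it is cheap and removes a choice that could otherwise be made after the results are seen.

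**What to change.** In section 5.2, state that the trial's conclusion rests on the ITT analysis with one fixed set of baseline covariates: baseline score, age, sex and baseline severity. Baseline score is an addition to the protocol's examples. Remove compliance from the covariates of the deciding model. Label the PP and unadjusted analyses supportive, unable on their own to support a claim of efficacy.

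Define the PP set by the 70% compliance threshold already in Drug Accountability plus deviations documented before unblinding. In section 3.2, say which analysis set the 166 refers to.

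With one version named, the rate for one scale and visit returns to 5%; the simulated unadjusted ITT test alone gave 5.1% to 5.4%. The cost is a few sentences, with no change to visits, recruitment or treatment. The downside for the sponsor is that a favourable PP or alternative-covariate result can no longer rescue a null ITT result.

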### **Procedures for discontinuation**

In case of premature termination or suspension of the trial, the coordinating chief investigator must inform the trial participants and ensure appropriate follow up and therapy. In addition, the regulatory authorities and ethics committee must be informed.

Participants may withdraw/discontinue from the study at will at any time without explanation. The participant may also be withdrawn at the discretion of the Investigator due to a safety concern or if judged non-compliant with trial procedures. Participants that withdraw/discontinue from the study will be asked to attend the end of treatment visit (Visit 8, Week 52) to monitor their safety, with a window period of up to 14 days of their withdrawal. The reason for withdrawal and date of withdrawal must be documented in the participant's source data file and electronic Case Report Form (CRF). All AEs and SAEs must be followed until resolution or stabilisation unless, in the Investigator's opinion, the condition is unlikely to resolve.

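### The ITT analysis fills missing scores by last value carried forward, although the planned linear mixed model does not need it and the filling biases the week-52 comparison

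*Protocol*

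**What the plan says.** Under Missing data and protocol violations (section 5.2), the protocol fixes the rule for the intention-to-treat (ITT) analysis: "Where data items are missing the last value carried forward method to replace missing data in the ITT analysis will be used". The rule stands in a paragraph on withdrawal, loss to follow-up and non-compliance, so it is not confined to single unanswered items. The same paragraph says that, for participants who die, "all measurements prior to death will be included in the analysis but all after death will be set to missing", and it encourages those who stop treatment to go on giving data.

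The subsection headed Primary efficacy analysis states: "The primary analysis will be linear mixed models through which we will test for differences between treatment groups on each outcome over time". Results are to be reported with 95% confidence intervals.

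Section 1.3 and Table 1 place on-treatment VaDAS-cog and ADCS-ADL at baseline, week 26 and week 52. Under Sample Size: "Allowing for a total non-compliance/withdrawal rate of 30%, 238 participants will be recruited into the trial across all centres", the aim being "to ensure 166 participants in the final analyses".

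Under Procedures for discontinuation, participants who withdraw "will be asked to attend the end of treatment visit (Visit 8, Week 52) to monitor their safety", within 14 days of withdrawal.

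**The concern.** A mixed model fitted to the observed scores already handles incomplete records, and is valid if data are missing at random. Filling the gaps first replaces that assumption with a stronger one: that a participant with dementia stops changing at the last visit attended. With a single on-treatment assessment before week 52, the filling is coarse. A loss before week 26 becomes two copies of baseline, and a loss between weeks 26 and 52 stops the clock halfway.

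Three things follow.

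- An effect that builds over time is shrunk.
- If the condition worsens and loss is unequal, the arm with more loss looks as if it declined less.
- The analysis counts copied values as measurements. The sample size plans on 166 analysed out of 238, whereas carrying forward analyses all 238 as if observed.

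Both primary scales are affected. The protocol chooses this method expressly, so an analysis plan that follows the protocol inherits it.

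**Working it through.** **Inputs from the protocol.** VaDAS-cog difference 3, SD 6.56; ADCS-ADL difference 3, SD 5.31; 1:1 allocation; 238 recruited, so 119 per arm; 30% combined non-compliance and withdrawal; efficacy scores at weeks 0, 26 and 52.

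**The plan's own figures reproduce.** A one-sided 5% two-sample t-test with 90% power (noncentral t) needs 166 in total for VaDAS-cog and 110 for ADCS-ADL. 166/0.70 = 237.1, which rounds up to an even 238.

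**Assumptions not in the documents.** Change is linear over 52 weeks. Half of those missing at week 52 were last seen at week 0 and half at week 26. Decline is 0 to 6 points a year.

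**1. Attenuation, equal loss.** Someone last seen at week 0 contributes none of the 52-week change, and someone last seen at week 26 contributes half. With a proportion m missing, the share kept is (1 − m) + (m/2)(0) + (m/2)(0.5) = 1 − 0.75m.

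| m | 3 × (1 − 0.75m) | Attenuation |
|---|---|---|
| 0.30 | 2.33 | 22% |
| 0.15 | 2.66 | 11% |
| 0.10 | 2.78 | 7.5% |

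This depends neither on the SD nor on the placebo decline, so it applies to both scales.

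**2. False difference, unequal loss, no true effect.** The difference is 0.75 × decline × (difference in m). With a 10 percentage-point difference in loss:

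- decline 0: 0
- decline 2: 0.75 × 2 × 0.10 = 0.15
- decline 4: 0.75 × 4 × 0.10 = 0.30
- decline 6: 0.75 × 6 × 0.10 = 0.45

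It favours the arm with more loss. With equal loss it is zero.

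**3. Error rate.** The 95% intervals imply a two-sided 5% test. For VaDAS-cog, SE = 6.56 × √(2/119) = 0.85. At 4 points a year the shift is 0.30/0.85 = 0.353 SE. The error is P(Z > 1.96 − 0.353) + P(Z < −1.96 − 0.353) = 0.054 + 0.010 = 6.4%. For declines of 2 and 6 it is 5.4% and 8.3%; for zero decline it stays at 5%.

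**4. Simulation.** There were 2,000 trials per scenario with 119 per arm, 30% total loss and an SD of 52-week change of about 6.56. A baseline-adjusted week-52 comparison after carrying forward was set against a likelihood-based repeated-measures model on observed data. Annual decline was 3 or 6 points, and data were missing completely at random or at random.

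| | Carried forward | Observed-data model |
|---|---|---|
| Estimate, true difference 3, equal loss | 2.28 to 2.36 | 3.00 to 3.04 |
| 95% CI coverage, same scenarios | 85–86% | 94–95% |
| Two-sided power, same scenarios | 85–88% | 88% |
| SE, all scenarios | 0.75 to 0.80 | about 0.97 |

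The SE with no missing data at all was 0.82 to 0.86.

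**The case against.** **Little turns on it for the test when loss is equal.** This stands. The estimate is smaller, but so is its SE, and simulated power is about the same under both methods. The harm is to the estimate and its interval.

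**The 30% is not a missing-data rate.** This stands. It combines non-compliance with withdrawal; non-compliers can still be assessed, and continued data collection is encouraged. Because Sample Size treats the whole 30% as absent from the analysis, it serves as an upper figure. The smaller rates are therefore shown too.

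**Decline and unequal loss are assumed.** This stands. The only placebo trajectory in the protocol, the 16-week pilot in section 2.3, shows ADAS-cog improving by 1.18 points. It is short and on a related scale, but it gives no support to any particular yearly decline, so the range starts at zero.

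**Stronger readings that the text does not carry:**

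- A reader might infer an error rate near 10%, by applying a one-sided test to the 0.30-point bias. The protocol adopts a one-sided test only to calculate sample size.
- A reader might infer that the SE is simply wrong. In the simulation it matches the sampling variability of the carried-forward estimator. It is too small only relative to the information observed at week 52.
- A reader might see a contradiction over deaths. The specific rule can be read as an exception to the general one; a clarifying clause is enough.
- A reader might infer that early-withdrawal scores are analysed as week 52. The protocol describes that visit as a safety visit and does not say so. If withdrawals were spread evenly, all attended and their scores were used that way, the target would be 0.70 × 3 + 0.30 × 1.5 = 2.55, so baseline copying would not be the mechanism for them.

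The lack of a sensitivity analysis for missing data is not counted as a fault, since it may stand in the analysis plan.

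**Conclusion.** The point holds in a limited form and should be fixed. The protocol prescribes single imputation that its own primary model does not need, and following the rule biases the week-52 contrast on both primary scales. Under linear change and the even timing split, a true 3-point difference is shrunk by 7.5% to 22% for 10% to 30% missing. With no true effect, the bias is zero under equal loss. It is 0 to 0.45 points for a 10 percentage-point difference in loss and a decline of 0 to 6 points a year, and it can favour either arm. The two-sided error is then about 6.4% at 4 points a year (5.4–8.3% for 2 to 6). The reported precision exceeds what the observed week-52 scores support.

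The size depends on the amount, timing and balance of loss and on the rate of decline, none of which the protocol gives. The existence of the rule and its mismatch with the model do not depend on them.

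**What to change.** Delete last value carried forward from the ITT analysis. Fit the planned mixed model, with time as a categorical variable, to all observed scores from all randomised participants, without single imputation. State that nothing is imputed after death. Add a sensitivity analysis for departures from missing at random, for example delta-adjusted or reference-based multiple imputation, in the protocol or in the analysis plan.

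As a clarification, reconcile Procedures for discontinuation with Missing data and protocol violations, so that efficacy scores from an early end-of-treatment visit are analysed at their actual study day and not as week 52.

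The cost is wording and a small amount of extra analysis. The SE will be somewhat larger, about 0.97 against 0.75 to 0.80 at 30% loss in the simulation, because it then reflects the data actually observed. Simulated one-sided power for a 3-point difference stays at about 91–94% (85–88% two-sided) with 238 recruited, so the sample size need not change on the protocol's own one-sided inputs.
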